## 4. ELIGIBILITY CRITERIA

### 4.1. Inclusion Criteria

Patients who meet the following inclusion criteria are eligible for admission into the study:

- Lumbar intrathecal catheter to be inserted as part of clinical hemodynamic management and CSF sample collected **within 48 hours of injury**
- Initial blood sample collected **within 24 hours of injury**
- Male or Female  $\geq 17$  (or the provincial age of majority – depending on local REB guidelines)
- Complete (AIS A) or incomplete (AIS B, C) acute traumatic spinal cord injury
- Bony spinal levels between C0 and T12 inclusive
- Blunt (non-penetrating) spinal cord injury treated either surgically or non-surgically
- Able to communicate in English, or with a translator where available, and provide informed consent

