### **Specific Aims**

This multicenter study will enroll 100 patients with acute traumatic cervical and thoracic SCI who have a lumbar intrathecal catheter inserted within 48 hours of their injury. The lumbar intrathecal catheter will be inserted pre-operatively for the measurement of ITP and the collection of cerebrospinal fluid (CSF) samples. SCPP will be calculated as the difference between MAP and the ITP.

There are two important distinct yet related objectives in this prospective interventional study.

1. Determine the effect of SCPP maintenance  $\geq 65$  mmHg in acute SCI on neurologic recovery as measured by ASIA Impairment Scale (AIS) grade conversion and motor score improvement.
2. Collect CSF and blood samples for the measurement of neurochemical biomarkers and storage for future biomarker discovery and validation studies.

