One observation from our first study of CSF drainage published in 2009 was that the pressure waveform was dampened in patients where the spinal cord was swollen against the dura, occluding the subarachnoid space [10]. We proposed that there was a pressure gradient established across the injury site in such circumstances, where the pressure at and above the injury site might be different than that measured below. Since then, there has been much ground-breaking work from Marios Papadopoulos who has confirmed this phenomenon of subarachnoid space occlusion by sliding a Codman pressure probe into the subarachnoid space between the dura and the swollen spinal cord, right at the injury site [23]. This raises the possibility that it may not be feasible to drain CSF or even measure the ITP at the injury site when the cord is swollen against the dura. We will therefore assess the pressure waveform over time

and determine if CSF drainage for SCPP management is even feasible if the pressure waveform is dampened (implying subarachnoid space occlusion).

Based on our experience, there is considerable variability in how much (and for how long) the cord swells, and how this affects the intrathecal pressure waveform. We also recognize that the spinal cord morphometry differs amongst patients, with some patients having a very large amount of CSF around their spinal cord and others having a very small amount of CSF around the cord. This difference in morphometry and – in essence – the native amount of “room” around the spinal cord will most likely influence whether the swollen spinal cord will be compressed by the dura. In Aarabi et al.’s MRI analysis of acute SCI patients after surgical decompression (published in Dec, 2018), they found that only 11% of patients had the combination of post-injury swelling and native cord morphometry to cause the cord to be swollen up against the dura even after a laminectomy [24]. Our published work from 2017 [11] is consistent with this, that despite the swelling that may occur at the SCI site, the lumbar intrathecal catheter still provides meaningful information about SCPP and has the advantage of technical familiarity with insertion of a lumbar intrathecal catheter without the potential hazards of inserting a catheter into the subarachnoid space right at the site of spinal cord injury.

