**Objective 4.** To determine if there are complications associated with the installation of the intrathecal catheter and drainage of CSF in the acute SCI patient.

It goes without saying that we will measure AEs associated with intrathecal catheter placement. Of course, acute SCI patients incur a huge number of AEs; but we have utilized a system of daily monitoring those that are most applicable to the lumbar catheters – namely CSF leak/postural headache, nausea/vomiting, and infection. The patients will be carefully monitored by the study research team throughout the time that they have the intrathecal catheter placed.

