## 5. STUDY PROCEDURES

### 5.1 Enrolment

Spinal cord injured patients will arrive at their respective trauma centers and, after being triaged and stabilized according to standard trauma protocols, the patients will be evaluated by staff (residents or fellows), and a complete neurologic examination will be performed using the International Standards for Neurologic Classification of Spinal Cord Injury (ISNCSCI) examination. The motor-sensory examination will be recorded and the AIS grade will be assigned.

SCI patients will be approached for enrolment in this study ***if the attending spine surgeon has decided that the insertion of a lumbar intrathecal catheter for monitoring ITP and maintaining SCPP is clinically indicated for their hemodynamic management.*** It is important to point out here that the decision to insert the lumbar intrathecal catheter for ITP monitoring and management is a clinical decision made by the surgical team. The rationale for the clinical decision to install a lumbar catheter is derived from our previous publication showing that SCPP is a more meaningful reflection of neurologic recovery than MAP [11]. Centers participating in this study are centers where the spine surgeons have adopted the insertion of the lumbar intrathecal catheter as part of the hemodynamic management of the acute SCI patient. This research protocol will seek to characterize how such active SCPP management influences neurologic outcome.

If the surgeon has decided to insert the intrathecal catheter and actively manage SCPP in the acute SCI patient, the patient will be approached to consider participating in the study. The potential research participant will be informed that the purposes of the study are to 1. evaluate their neurologic recovery over time, 2. obtain CSF and blood samples for biomarker studies, 3. obtain CSF and blood samples for storage in the International Spinal Cord Injury Biobank (ISCIB).

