### **5.4.1. CSF Sampling and Processing**

A 6 ml sample of CSF will be obtained at the time of lumbar intrathecal catheter insertion. For subsequent CSF samples obtained post-operatively, a 6 ml sample will be aspirated from the intrathecal catheter.

The 6 ml CSF sample will be divided into 1.5 ml Eppendorf tubes, and then centrifuged at 2000 RCF (or g) for 10 minutes at room temperature. These parameters for CSF centrifugation were recommended in 2014 by the Biomarkers for Alzheimer’s and Parkinson’s disease (BIOMARKAPD) European multicenter consortium [27]. The supernatant will then be pipetted off in 200 ul increments into pre-labelled 250 ul polypropylene tubes and immediately frozen in an ethanol-dry ice bath and stored at -80°C.

As per the BIOMARKAPD recommendations, it will be endeavored to keep the time between sample acquisition and freezing below 2 hours.

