## Schedule of Procedures

| Procedure                          | Enrolment      | Catheter Insertion                         | T 24 h         | T 48 h | T 72 h | T 96 h | T 120 h | T 144 h | T 168 h        | 24 hrs post ITC removal          | Month 3 e (+/- 2 weeks) | Month 6 e (+/- 2 weeks) | Month 12 e (+/- 4 weeks) |
|------------------------------------|----------------|--------------------------------------------|----------------|--------|--------|--------|---------|---------|----------------|----------------------------------|------------------------------------|------------------------------------|-------------------------------------|
| Informed consent                   | X              |                                            |                |        |        |        |         |         |                |                                  |                                    |                                    |                                     |
| Eligibility criteria review        | X              |                                            |                |        |        |        |         |         |                |                                  |                                    |                                    |                                     |
| Medical history                    | X              |                                            |                |        |        |        |         |         |                |                                  |                                    |                                    |                                     |
| Demographics                       | X              |                                            |                |        |        |        |         |         |                |                                  |                                    |                                    |                                     |
| ISNCSCI assessment                 | X              |                                            | X              | X      | X      | X      | X       | X       | X              |                                  | X                                  | X                                  | X                                   |

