## 7. SAFETY / ADVERSE EVENTS

In the previous CAMPER trial, there were no documented cases of CSF leakage, headache, neurologic deterioration, or meningitis attributable to the insertion, presence, or withdrawal of the lumbar intrathecal catheter. **In this CASPER trial, patients will have the intrathecal catheter inserted as part of their clinical management.** However, as part of the clinical follow-up of participants enrolled in CASPER, we will document AEs related to the insertion, presence, or withdrawal of the lumbar intrathecal catheter, and also related to the drainage of CSF to lower ITP. These specific AEs are described further in Section 7.3.

The AE reporting period will be defined as commencing from the time of insertion of the intrathecal catheter until 24 hours after its removal. If an AE is ongoing at the time of catheter removal, it will be monitored until resolution or until 30 days have elapsed.

A review and sign-off by the local Principal Investigator of any AEs related specifically to the presence of the intrathecal catheter will occur for each individual patient at the end of the 24 hours following intrathecal catheter removal. A data safety monitoring board will be established to perform an interim analysis of all complications related to insertion and presence of a lumbar intrathecal catheter and will convene after the first 10 patients enrolled, and then again after 50 patients have been enrolled.

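### Section 4.1 makes eligibility depend on a CSF sample that only a successful insertion can yield, so the installation part of Objective 4 can lose failed attempts

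*Protocol*

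**What the plan says.** Section 4.1 lists as its first condition for admission: "Lumbar intrathecal catheter to be inserted as part of clinical hemodynamic management and CSF sample collected", with a limit of 48 hours from injury. Specific Aims describes the 100 patients in similar terms, as those "who have a lumbar intrathecal catheter inserted within 48 hours of their injury".

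Other sections put enrolment earlier. Section 5.1 states: "If the surgeon has decided to insert the intrathecal catheter and actively manage SCPP in the acute SCI patient, the patient will be approached". In the Schedule of Procedures, consent and the row "Eligibility criteria review" are marked in the Enrolment column, which comes before Catheter Insertion. Section 5.4.1 fixes when the first sample is taken: "A 6 ml sample of CSF will be obtained at the time of lumbar intrathecal catheter insertion".

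Objective 4 in section 3 reads: "To determine if there are complications associated with the installation of the intrathecal catheter and drainage of CSF in the acute SCI patient". Section 7 defines the adverse event reporting period as "commencing from the time of insertion of the intrathecal catheter until 24 hours after its removal". Section 7.3.2 says that the needle, as well as the catheter, can injure lumbosacral nerve roots.

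**The concern.** The criterion joins a planned event (a catheter that is to be placed) to a completed result (a sample that has been collected). The result cannot be verified when eligibility is reviewed, and it can be met only if the procedure succeeds. A consented patient with a failed or dry attempt, and no CSF by 48 hours, does not satisfy the criterion as written. The protocol has no rule on whether that patient stays in, is replaced, or counts for safety, so sites may handle the case differently.

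What is at stake is the installation part of Objective 4. Harm from the needle does not require a catheter to end up in place. If failed attempts leave the cohort, they leave both numerator and denominator, and the reported rate describes successful installations rather than all patients in whom installation was tried.

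**Working it through.** The protocol states no figure on this point, so there is none to reproduce. The check is one of sequence and text, followed by an illustration.

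**Sequence**

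1. The surgeon decides to insert a catheter and the patient is approached (section 5.1).
2. Consent and eligibility review take place (Schedule of Procedures, Enrolment column).
3. Insertion is attempted (next column).
4. If it succeeds, the first 6 ml CSF sample is drawn (section 5.4.1).

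The criterion in section 4.1 depends on step 4 but is applied at step 2. A patient who stops at step 3 has consented and been exposed to the needle, but does not meet the criterion as written.

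**Safety follow-up of a failed attempt**

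- The reporting window opens at insertion and closes 24 hours after removal (section 7). With no catheter left in place there is no removal, so the closing time is undefined.
- The daily ISNCSCI examination to detect deterioration is tied to the catheter being in place (section 6.1).
- The safety board meets after 10 and after 50 enrolled patients (section 7), so the meaning of enrolled determines what it sees.

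**Illustration of size**

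The protocol gives neither the share of attempts that fail, *f*, nor the complication risk in failed attempts, *p_fail*. Both are assumed here. The risk in successful insertions, *p_succ*, is set to 1% as a placeholder. The protocol's only estimate of about 1% is for meningitis (section 7.3.4), not for installation.

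- Attempts behind 100 retained patients = 100 / (1 - *f*)
- All-attempt rate = (1 - *f*) × *p_succ* + *f* × *p_fail*

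| *f* | Failed attempts per 100 retained | Rate if *p_fail* = 1% | if 5% | if 10% |
|---|---|---|---|---|
| 2% | 2.0 | 1.00% | 1.08% | 1.18% |
| 5% | 5.3 | 1.00% | 1.20% | 1.45% |
| 10% | 11.1 | 1.00% | 1.40% | 1.90% |
| 15% | 17.6 | 1.00% | 1.60% | 2.35% |

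Worked row: at *f* = 10% and *p_fail* = 10%, 0.90 × 1% + 0.10 × 10% = 1.90%, against 1% in the retained patients. The unseen events number 11.1 × 0.10 = 1.1 per 100 retained patients. At *p_fail* = *p_succ* the ratio is 1.00 for every *f*.

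For needle injury alone, section 7.3.2 cites a neuraxial injury risk of 0.001% to 0.07%. At the upper end and *f* = 10%, the unseen events number 11.1 × 0.0007 = 0.008.

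**The case against.** The strongest reply is that no exclusion is intended. The criterion says the catheter is to be inserted, so the 48 hours can be read as a time window for planned procedures. Section 5.1 and the schedule support enrolment before insertion, and section 5.4.1 already treats sampling as a study procedure. No text says that a consented patient with a failed insertion is withdrawn or replaced. This stands in part: exclusion is the literal reading, not an explicit rule. But a criterion open to both readings, with no rule for the failed case, still needs correcting in a multicentre study.

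Three stronger readings are tempting, and the protocol does not support them.

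- *Objective 3 is compromised too.* A reader might infer this because section 3 warns that "it may not be feasible to drain CSF or even measure the ITP at the injury site". That objective, however, asks whether drainage works when the cord is swollen against the dura, judged from the pressure waveform over time. It presupposes a working lumbar catheter. One sample within 48 hours does not remove patients whose waveform dampens or whose drainage fails later. Multiplying an assumed drainage success rate by (1 - *f*) would mix two different quantities.
- *Harm from a failed attempt falls outside reporting altogether.* Reporting starts at insertion, the schedule marks adverse events in the insertion column, and section 5.2 describes insertion as including the needle pass. Section 7.1.4 also requires all SAEs during the study to be reported. Only the end of the window is undefined.
- *Installation harm is materially understated.* Any percentage rests on assumed inputs. With the needle-injury figures the protocol cites, the expected loss is far below one event.

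It may also be said that safety denominators belong in a statistical analysis plan, which is not shown here. Eligibility and the recording of events are fixed in the protocol, though, and a later plan cannot recover attempts that were never recorded.

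**Conclusion.** The point holds in a limited form. Section 4.1 ties eligibility to an event that follows eligibility review and requires the procedure to succeed. Taken literally, that selects on success of the procedure whose safety Objective 4 assesses. The reporting window has no defined end for a failed attempt.

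The size cannot be derived from the document. It runs from no bias, if failed attempts carry the same risk as successful ones, to an all-attempt rate about 1.2 to 2.4 times the reported one under the assumed 2-15% failures and 10% versus 1% risks. In absolute terms this is at most about two unseen events per 100 retained patients (17.6 × 0.10 = 1.8). Complications of dwell, drainage and removal, and Objective 3, are largely unaffected. The Objective 1 comparison with CAMPER does not depend on this point if it keeps the catheter-in-place population. The change is worth making because it is cheap and the information cannot be recovered later.

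**What to change.** - Define eligibility by the clinical decision to insert plus consent, with insertion planned within 48 hours of injury. Align the description of the 100 patients in Specific Aims.
- Move CSF collection out of section 4.1 and keep it as a study procedure under section 5.4.
- Record every attempted insertion and its outcome on the case report form.
- In section 7, define when the adverse event window ends if no catheter is left in place.
- Report installation complications over all attempted insertions.
- Show failed insertions separately in the patient flow, not as Objective 3 failures.
- Keep the catheter-in-place population for the Objective 1 comparison with CAMPER, and state whether the 100 counts enrolled patients or patients with a catheter in place.

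The cost is a short eligibility amendment, a sentence in section 7 and one attempted/failed field on the form. The downside is that a few enrolled patients will contribute no CSF or SCPP data. If 100 patients with a catheter in place are wanted, the assumed 2-15% failures imply about 102 to 118 attempts.

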## 2.4. The Canadian Multicenter CSF Pressure and Biomarker Study (CAMPER)

Following the findings of our small prospective randomized clinical trial on CSF drainage, a decision was made to make the study a prospective observational trial whereby we inserted the lumbar intrathecal catheters but only observed ITP and SCPP (rather than actively draining CSF to reduce ITP). This protocol was initiated locally at Vancouver General Hospital, and then expanded to four other hospitals in: London, Ontario; Halifax, Nova Scotia; Montreal, Quebec; and San Francisco, California.

Inclusion criteria included: cervical or thoracic SCI, admitted within 48 hours of injury, and the ability to obtain a neurologic assessment and informed consent (thus excluding those with head injuries or multi-trauma). The CAMPER protocol involved the insertion of a lumbar intrathecal catheter and the monitoring of ITP for 5 days. No active measures were conducted to change the ITP by draining CSF. CSF and blood samples were obtained approximately 3 times per day for biomarker studies.

In 2017 we reported on the ITP, SCPP, and MAP data and how this related to neurologic outcome. This cohort included 91 patients: 72 males, 19 females, 54 cervical, 37 thoracolumbar, and 57 AIS A, 17 AIS B, and 17 AIS C for whom we had 6 month follow-up data [11].

Firstly, we mapped out every recorded MAP, ITP (or CSF Pressure, “CSFP”), and SCPP for every patient throughout the entire period of time they had the lumbar drain in ([Figure 3](#)).

**Figure 3.** MAP, CSFP, and SCPP over 5 days in all patients.

[figure not shown]

Then, we examined neurologic outcome with respect to AIS grade conversion at 6 months post-injury. We looked at every single recorded MAP, ITP, and SCPP, and examined whether each of these data points was related to AIS grade conversion, or no conversion. This enabled us to generate “transition points” at which point the chance of AIS Grade conversion versus the chance of no AIS Grade conversion was EQUAL (i.e. The ‘relative risk’ of not improving versus improving an AIS grade was 1.0). For MAP, CSFP, and SCPP these transitions points occurred at 70, 29, and 50 mmHg, respectively (**Figure 4**).

**Figure 4.** Relative risk of not improving an AIS grade. Here, one can appreciate that the relative risk of not improving an AIS grade increases as the MAP and SCPP decreases, and as the CSFP increases.

[figure not shown]

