## **5.4 CSF and Blood Collection and Processing for Biomarker Studies and Biobank Storage**

An important aspect of the prospective non-randomized design of the CASPER study is the evaluation of CSF biomarkers to help interpret neurologic recovery and distinguish therapeutic effect from spontaneous recovery. Because participants who are enrolled in this study will have a lumbar intrathecal catheter inserted, there will be the opportunity to obtain CSF samples for biomarker studies. The collection of parallel blood samples for biomarker studies will be achieved through a pre-existing arterial line or central venous catheter.

Sample collection for CSF and blood will occur at the time of lumbar intrathecal catheter insertion and then 3 times per day for the subsequent 7 days that the catheter is in place. A “complete set” of CSF and blood samples will therefore include 21 samples of each biofluid. In an attempt to “standardize” the time of CSF and blood collection, at least one sample per day will be acquired as close as possible to the 24, 48, 72, 96, 120, 144, and 168 hour time point. So, for example, if the subject has the lumbar intrathecal catheter inserted at 19 hrs post-injury, the first CSF sample will be drawn at 19 hrs post-injury, but then another sample will be drawn 5 hours later at 24 hrs post-injury.

In addition, blood samples will be collected at the time of the 3, 6 and 12 month study follow-up visits.

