#### **5.4.2. Serum and Plasma Collection and Processing.**

At the same time as the CSF sample is collected, a 15 ml sample of blood will be drawn. This will be divided in thirds: 5 ml for serum, 5 ml for plasma, and 5 ml for RNA isolation. The rationale for this division into both serum and plasma is that some analyses may be better suited for serum samples, while others might be better suited for plasma. In order to provide these options for future analyses, the blood sample will be processed for both. Further, a 15 ml blood sample will be collected at the 3, 6 and 12 month study follow-up visit time points.

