| MAP, ITP, SCPP Monitoring          |                | PERFORMED THROUGHOUT INSERTION OF CATHETER |                |        |        |        |         |         |                |                                  |                                    |                                    |                                     |
| SCIM-III                           |                |                                            |                |        |        |        |         |         |                |                                  | X                                  | X                                  | X                                   |
| Adverse events                     |                | X                                          | X              | X      | X      | X      | X       | X       | X              | X
(Also 6h after ITC removal) |                                    |                                    |                                     |

- CSF and blood samples are collected daily at approximately 8-hour intervals from the time of insertion. When possible, one of the scheduled sample collection time points will be adjusted to correspond to the 24, 48, 72, 96, 120, 144, 168 hours post-injury time points (i.e. days 1 through 7 post-injury)
- CSF cell count, culture (and sensitivity), protein and glucose are clinical assessments required for patients with lumbar drains. These assessments and the timing of them may vary according to hospital-specific protocols. Individual hospital protocols will be followed. At VGH, patients with lumbar drains typically have one “clinical” sample sent each day for analysis in the lab.
- Baseline pain assessment to be performed prior to administration of medications for neuropathic pain, if possible. Timing will be dependent on ability to assess and ideally will take place as soon as possible following patient enrollment. Date of administration will be recorded as well as whether or not the patient is taking pain medications. Further pain assessments to be performed daily for 7 days following intrathecal catheter (ITC) insertion, again, whenever assessment is physically possible.
- Shipment of samples to central laboratory (VGH) after removal of lumbar ITC.
- Study visit windows are included for guidance. Site visits may occur outside these windows. Contact CASPER project manager as needed.
- Study sites will follow their standard clinical practice in the use of vasopressors.

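### Initial blood is required within 24 h of injury but scheduled only at catheter insertion, which is allowed up to 48 h, so the entry window and its comparability with CAMPER are unsettled

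*Protocol*

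**What the plan says.** Section 4.1 lists two separate timing criteria, and a patient must meet both:

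- The first, on catheter and CSF, reads: "Lumbar intrathecal catheter to be inserted as part of clinical hemodynamic management and CSF sample collected within 48 hours of injury".
- The second, which concerns blood, sets a shorter limit: "Initial blood sample collected within 24 hours of injury".

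The Specific Aims in Section 1 repeat the longer limit, describing patients "who have a lumbar intrathecal catheter inserted within 48 hours of their injury".

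The sampling text ties first blood to the catheter. Section 5.4 states: "Sample collection for CSF and blood will occur at the time of lumbar intrathecal catheter insertion". Section 5.4.2 pairs each blood draw with CSF: "At the same time as the CSF sample is collected, a 15 ml sample of blood will be drawn". In the Schedule of Procedures, the blood row has its first mark under Catheter Insertion and nothing under Enrolment, and a footnote reads "CSF and blood samples are collected daily at approximately 8-hour intervals from the time of insertion".

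Section 7.3.3, on thromboembolic prophylaxis, gives yet another timing. It takes as fact that the catheter is in place by 24 h after injury.

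Section 10 makes CAMPER the control group for the primary comparison. Section 2.4 summarises CAMPER entry as "cervical or thoracic SCI, admitted within 48 hours of injury", with no time limit on a blood sample. The Analysis Plan in Section 10 lists AIS grade, neurologic level, baseline motor score, 24 h CSF biomarkers, age and gender as anticipated covariates. Time from injury to admission, catheter or surgery is not listed.

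**The concern.** Two mandatory criteria give different time limits for samples that the rest of the protocol collects together. A site cannot tell whether a patient catheterised after 24 h is eligible. One site may screen such patients out, another may enrol them and record a deviation, and a third may take an unscheduled early blood sample. The entry window would then depend on local interpretation.

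In a randomised trial this would be mainly a nuisance, since both arms would share the same rule. Here the comparison is with an external cohort, so an entry rule that acts on only one side can create a difference between the groups. The protocol's own background treats early hours as important. Section 2.1 says early decompression appears to improve outcome in cervical injury, and Section 2.4 reports that exposure to low SCPP separated converters from non-converters particularly in the first 24 hours. If CASPER in effect takes patients reached earlier than some CAMPER controls, part of an observed difference in motor recovery could reflect time to care rather than SCPP management.

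**Working it through.** There is no stated figure to reproduce. The check is a logical one on the timing rules.

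**Notation (hours from injury).** Tc is the time of catheter and first CSF, Tb the time of first blood, and Ta the time the patient is admitted or first reached.

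**Inputs**

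| Source | Rule |
|---|---|
| Section 4.1, first criterion; Section 1, Specific Aims | Tc ≤ 48 |
| Section 4.1, second criterion | Tb ≤ 24 |
| Sections 5.4 and 5.4.2, Schedule of Procedures | Tb = Tc |
| Section 7.3.3 | Tc ≤ 24, stated as fact |
| Section 2.4 (CAMPER) | Ta ≤ 48, no limit on Tb |

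**Reading 1: the schedule is followed.** With Tb = Tc, the two criteria become Tc ≤ 48 and Tc ≤ 24. Together they give Tc ≤ min(48, 24) = 24 h. The 48 h limit then never applies.

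**Reading 2: blood may be drawn before the catheter.** Tb is then separate from Tc, and both limits can operate. A patient cannot be sampled before being reached, so Ta ≤ Tb ≤ 24 and therefore Ta ≤ 24 h. The catheter may follow up to 48 h.

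**Types of patient under each rule**

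| Patient | CASPER, reading 1 | CASPER, reading 2 | CAMPER time rule as described |
|---|---|---|---|
| Catheter at 19 h (the example in Section 5.4) | eligible | eligible | admitted |
| Reached before 24 h, catheter at 30 h | fails on blood | eligible if an early draw is made | admitted |
| First reached between 24 and 48 h | fails on blood | fails on blood | admitted |
| Admitted by 48 h, catheter after 48 h | fails on catheter | fails on catheter | not excluded by the admission limit |

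The second row shows that eligibility depends on an unstated choice about when blood may be drawn. The third row does not depend on that choice: such patients are outside CASPER and inside CAMPER's described limit on either reading. The last row shows that the two 48 h limits run on different clocks.

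**Internal consistency.** Under reading 1, Section 7.3.3 agrees with the effective 24 h limit, but Section 1 and the first criterion in Section 4.1 do not describe it. Under reading 2, Section 1 and Section 4.1 agree, but Section 7.3.3 does not, and Section 5.4, Section 5.4.2 and the schedule omit the required draw. On neither reading do all the statements describe one procedure.

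**The case against.** The best defence is that the two criteria were meant to differ. They sit next to each other with different limits, which suggests that blood was expected to be obtainable before the catheter. Section 5.4 says blood collection will be "achieved through a pre-existing arterial line or central venous catheter", so the intrathecal catheter is not needed for it. Under Section 5.1 patients are approached once the surgeon has decided to insert the catheter, which leaves time for a draw before insertion. This stands to the extent that the collapse to 24 h is one reading and not a certainty. It does not remove the problem, because no procedure schedules the earlier draw and patients first reached after 24 h stay excluded.

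The defence is also right on several stronger inferences that a reader might make:

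- *That CASPER's window is half of CAMPER's.* CAMPER's 48 h is time to admission and CASPER's is time to catheter and CSF. The two are not comparable as a ratio, and Section 2.4 is a summary of CAMPER's criteria, not its protocol.
- *That a countable share of the 100 patients is lost.* The documents give no distribution of insertion times. The 100 is an enrolment target, so a stricter rule affects screening and accrual time, not the number enrolled. Section 7.3.3 suggests that late insertions may be few.
- *That the blood rule causes missing 24 h CSF values.* Any such gap comes from the 48 h limit on CSF, whatever the blood rule says.

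Finally, the covariates are described only as anticipated, and an analysis plan may add time from injury. That is fair: the short list is not a fault in itself. The eligibility and sampling text, however, belongs to the protocol and is inconsistent there.

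**Conclusion.** The point holds as an inconsistency in eligibility and sampling with a plausible consequence for the primary comparison. If first blood is taken at insertion, as scheduled, the effective catheter window is 24 h and patients catheterised at 24–48 h fail entry. If an earlier draw is intended, the protocol does not provide for it. On both readings, patients first reached after 24 h are excluded from CASPER but fall within CAMPER's described admission limit, and no listed covariate captures time from injury.

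The cohorts may therefore differ in time to care. A reader might infer that they do differ, and that the difference favours CASPER. The documents do not show this: they give neither cohort's admission or insertion times, and an upper limit on entry says nothing about how patients are distributed below it. The size cannot be computed. The conclusion rests on two assumptions: that both criteria in Section 4.1 are binding, and that Section 2.4 fairly summarises CAMPER's time limit. The amendment is worth making because it is cheap and removes an avoidable source of non-comparability.

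**What to change.** 1. Reconcile the timing of first blood and catheter across Section 1 (Specific Aims), Section 4.1, Section 5.4, Section 5.4.2, the Schedule of Procedures and Section 7.3.3, so that all describe one entry window. Which window applies is for the sponsor and investigators to decide.
2. If a blood draw before catheter insertion is intended, say so in Section 5.4 and add it to the schedule.
3. Apply the resulting time-from-injury window to the CAMPER control records on the same clock, or adjust the primary comparison for time from injury.

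The cost is a short amendment and either an eligibility filter on existing CAMPER records or one more covariate. The filter may leave a few fewer controls. Either option needs CAMPER's times from injury, which the protocol does not report and which should be confirmed as available.
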